# *DE*ep *VE*in *L*esion *OP*timisation (DEVELOP) trial: protocol for a randomised, assessor-blinded feasibility trial of iliac vein intervention for venous leg ulcers

**DOI:** 10.1186/s40814-021-00779-2

**Published:** 2021-02-04

**Keywords:** Venous ulcer, Endovenous, Deep venous intervention, Iliac vein, Intra-vascular ultrasound, Saphenous incompetence

## Abstract

**Background:**

Venous leg ulceration is a widespread, debilitating pathology with high recurrence rates. Conservative treatment using graduated compression dressings may be associated with unacceptable ulcer recurrence rates. Early superficial venous ablation encourages ulcer healing and reduces recurrence. However, many of this cohort display concomitant ilio-caval stenosis, which further contributes to lower limb venous hypertension and ulceration.

An approach that combines early superficial venous ablation with early treatment of ilio-caval stenotic disease may significantly improve ulcer healing and recurrence rates. We question whether early iliac vein interrogation with intravascular ultrasound (IVUS), stenting of significant occlusive disease plus superficial venous ablation, in patients with active venous leg ulceration, will produce superior ulcer healing to standard therapy.

**Methods:**

This is a prospective, multi-centre, randomised controlled, feasibility trial recruiting patients with lower limb venous ulceration and saphenous venous incompetence. Patients will be randomised to undergo either truncal ablation and compression therapy or truncal ablation, simultaneous iliac interrogation with intravascular ultrasound and stenting of significant (> 50%) iliac vein lesions plus compression therapy. The primary feasibility outcome will be the rate of eligible patient participation while the primary clinical outcomes will be ulcer healing and procedural safety. Secondary outcomes include time to healing, quality of life and clinical scores, ulcer recurrence rates and rates of post-thrombotic syndrome. Follow-up will be over a 5-year period. This feasibility trial is designed to include 60 patients. Should it be practicable a total of 594 patients would be required to adequately power the trial to definitively address ulcer-healing rates.

**Discussion:**

This trial will be the first randomised trial to examine the role iliac interrogation and intervention in conjunction with standard operative therapy in the management of venous ulceration related to superficial truncal venous incompetence.

**Ethical committee reference:**

C.A. 2111 Galway Clinical Research Ethics Committee

**Registration:**

Clinical Trials.gov registration NCT03640689, Registered on 21 August 2018.

**Supplementary Information:**

The online version contains supplementary material available at 10.1186/s40814-021-00779-2.

## Background

Leg ulcers are a widespread, debilitating problem with a prevalence in Ireland of 0.12% overall. This increases to 1% among patients over 70 years of age. Recurrence is common with 12-month healing rates reported between 16 and 36% [1]. The majority of these leg ulcers (81%) are venous in origin and are treated in the community by public health nurses at a significant annual cost [2].

Typically chronic venous hypertension results in lower limb skin changes, often at the level of the ankle. Oedema, fibrin pericapillary cuffs and/or trapping of white cells within the interstitium typically precede tissue loss with these changes leading to skin ulceration as a result of relative local tissue hypoxia or cytokine/protease release [3, 4].

The mainstay of treatment of leg ulcers is the application of graduated compression to the limb with the aim of promoting venous return, reversing venous hypertension and the local tissue changes, thus allowing the ulcer to heal. Maximum compression is applied at the ankle with gradually lesser compression being applied proximally up the leg. Graduated compression bandaging is usually used to achieve ulcer healing while compression stockings are fitted to prevent recurrence. A Cochrane review of the management of leg ulcers concluded that compression increases ulcer healing rates compared to no compression, multi-layered systems are more effective than single-layered systems and that high compression was better than low compression [5]. Nevertheless, in spite of the application of best evidence-based therapy, healing rates for venous leg ulcers remain disappointing at 50% to 70% following 12 weeks of treatment [6].

With an increasingly elderly population, the incidence of venous ulceration is likely to rise. The negative impact of leg ulceration on patients’ quality of life and on healthcare costs is well recognised [7–9]. Increased prevalence combined with poor reported healing rates and high incidence of ulcer recurrence makes the development of a new treatment which could accelerate healing rates beyond that currently achieved using compression bandaging most desirable.

## Trial rationale

Traditionally, venous reflux was viewed as the primary causative factor in venous ulceration. Treatment strategies such as compression or, more recently, early superficial venous ablation [10] aim to address the reflux and thereby encourage ulcer healing. However, advances in imaging techniques have revealed that ilio-caval venous obstruction occurs frequently in patients with chronic venous disease [11, 12]. Moreover, endovascular treatment of ilio-caval occlusive disease produces significant symptomatic improvement even in the presence of persistent uncorrected deep venous reflux [13].

Two recent systematic reviews have concluded that endovascular stent placement for iliac-caval venous obstruction is safe with high technical success rates [14, 15]. Non-thrombotic iliac vein lesions (NIVLs) are present in up to 80% of patients with symptomatic venous disease [16]. These lesions are characterised by their non-thrombotic aetiology and often are identified at post-mortem as intravascular adhesions or membranes. Commonly, they are in the form of a web and may progress to venous occlusion or contribute to increased lower limb venous pressures. These obstructive lesions, along with post thrombotic stenoses, are left unaddressed by current ulcer treatment strategies, which focus solely on the reflux component of the underlying venous hypertension. This predisposes to persistent venous hypertension, in turn leading to recurrent superficial venous reflux and an increased risk of recurrent ulceration. This focus solely on the reflux component may explain the relatively limited improvement in ulcer healing rates in studies of early venous ablation [10].

An approach which combines early superficial venous ablation with early treatment of iliac occlusive disease, i.e. addresses both the reflux and obstructive components of the disease, could significantly improve ulcer healing and recurrence rates. Iliac vein interrogation and stenting if appropriate undertaken simultaneously with superficial venous ablation has the potential to significantly improve ulcer healing rates.

Thus, we ask, that in patients with active venous leg ulceration does early iliac vein interrogation with intravascular ultrasound (IVUS), stenting of significant occlusive disease plus superficial venous ablation produce superior ulcer healing to compression therapy plus superficial venous ablation alone?

## Objectives

The single main research question for this feasibility trial is as follows: in adult patients with venous ulceration and saphenous vein incompetence is iliac vein assessment with IVUS and stenting (of significant occlusive disease) in addition to saphenous venous ablation and compression feasible and acceptable to patients with venous ulceration?

### Primary objective

The primary obective is to determine the proportion of suitable patients with venous ulceration who agree to randomisation to either superficial venous ablation plus early iliac vein interrogation plus endovascular stenting in the presence of significant occlusive disease or to superficial venous ablation plus compression therapy alone.

### Secondary objectives

The secondary objectives are the following:
To determine the relative performance of duplex ultrasound compared to IVUS for the prediction of occult iliac diseaseTo determine the rate of primary or recurrent ulceration up to 5 years following interventionTo assess patient quality of life in the short and medium term following each mode of interventionTo determine what proportion of patients require iliac vein stenting on the basis of IVUSTo determine the outcomes of routine IVUS in patients with venous ulcerationTo determine the safety of routine IVUS and/or iliac vein stenting

## Trial design and endpoints

### Statement of design

This is a prospective randomised controlled, assessor-blinded, feasibility trial with participants allocated to one of two parallel groups in a 1:1 fashion. The primary trial centres will be the University Hospital Galway, Ireland, and Singapore General Hospital with further centres currently being evaluated for inclusion. Both the Departments of Vascular Surgery and Interventional Radiology will conduct the trial in unison with equal oversight. Suitable patients shall be recruited from both the outpatient and inpatient setting.

### Outcomes

#### Primary feasibility outcome

The primary feasibility outcome of this study will be the proportion of eligible patients with venous ulceration who agree to proceed with intervention and undergo randomisation. The proportion of eligible patients for inclusion will also be recorded to inform the rate of potential recruitment. An acceptance rate of 50% among those eligible will be deemed feasible.

#### Primary efficacy outcomes

The primary efficacy outcome will be the proportion of ulcers healed 3 months following the overall intervention and the iliac vein patency in the interventional group.
A healed ulcer is defined as complete re-epithelialization with no scab and no requirement for dressing [17].

Stent patency will be evaluated by ultrasound within 24 h, at 6 months, 1 year and annually thereafter. One-year patency rates will be reported alongside the primary efficacy endpoint. Five-year patency rates will be reported in a separate long-term follow-up report. The following will be reported with respect to patency:
Primary patency: patent stent with less than 20% in-stent or between stent stenosis and no re-interventionsPrimary assisted patency: patent stent with less than 20% in-stent or between stent restenosis which has undergone re-intervention to prevent occlusionSecondary patency: patent stent which has been reopened following occlusionStent occlusion: stent with a no-flow segment which has not undergone re-intervention or in which re-intervention failed

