## Trial population

### Inclusion criteria

Consenting patients, aged 18 and over, with ultrasound detected great or short saphenous venous incompetence with an associated primary or recurrent lower limb venous ulcer(s) will be eligible for inclusion. Saphenous reflux is defined as retrograde flow > 0.5 s in superficial vein [17].

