### Randomisation

Following the consent process randomisation will be undertaken using sequentially numbered opaque sealed envelopes administered by an independent research assistant in the Lambe Institute, University Hospital Galway, allowing for allocation concealment. A unique trial number will be assigned to each individual at the time of randomisation. Patients will be randomised to one of two groups.

Group 1: Compression bandaging and endovascular treatment of saphenous truncal incompetence.

Group 2: Compression bandaging, endovascular treatment of saphenous incompetence with simultaneous iliac vein interrogation with IVUS and stenting if an occlusive lesion > 50% is identified.

A designated member of the research team who will not be involved with data collection will have access to the randomisation data and arrange intervention and investigation as required. There will be no sham intervention.

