#### Ulcer assessment

The ulcer will be evaluated by an assessor who has been blinded to the treatment allocation of the patient. Wound size will be calculated using digital planimetry and recorded as cm^2^. Wound assessment will be evaluated using the Bates-Jensen wound assessment tool which has been validated for use in venous leg ulcer assessment [18, 19]. Ulcers that heal prior to intervention will be analysed with intention to treat (Fig. 1).

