## Interventions

### Endovenous ablation and IVUS procedure

All procedures will be carried out by either a vascular surgeon or interventional radiologist with significant experience in both endovenous ablation and IVUS (Visions 0.035, Philips, Amsterdam). The aim is for ablation within 4 weeks of randomisation. All patients will undergo endovenous ablation of refluxing axial superficial veins in the affected leg using thermal or non-thermal ablative techniques under local anaesthesia. Modality of intervention will be at the discretion of the operator. Control procedures will be undertaken in an ambulatory care setting while the interventional group will be managed in an operating theatre or interventional suite. All procedures will be completed under local anaesthesia.

The ablation procedure will be performed simultaneously with IVUS and stenting where applicable. A 9F access sheath will be placed under ultrasound guidance in the saphenous vein at the lowest point of reflux to allow introduction of firstly the IVUS catheter into the ipsilateral common iliac, external iliac and common femoral veins followed by the ablation probe. If the IVUS cannot be passed, the common femoral or jugular vein will be cannulated at the discretion of the operator. Iliac vein interrogation using the IVUS will be undertaken to determine the degree of area luminal area reduction (LAR) at each of the known arterial and ligamentous crossing points on the affected side which predispose to NIVL formation. These include the left and right proximal common iliac veins (where crossed by the right iliac artery), the right and left proximal external iliac vein (where crossed by the external iliac arteries and the retro-inguinal regions.

The LAR will be determined by comparison of the minimal luminal area at the NIVL site to the anatomical minimum for the respective vein, as recommended by experts in the field [22]. Area will be calculated using the standard mathematical formula Area = *A* = *πr*^2^. The reference area values for the iliac veins and the common femoral veins are detailed in Table 1. Lesions will be classified into the degree of stenosis by luminal area as detailed in Table 2.

**Table 1 Tab1:** Normal anatomical reference values for deep veins

Vein	Normal minimum diameter	Normal minimum area
**Common iliac vein**	16 mm	201 mm^2^
**External iliac vein**	14 mm	154 mm^2^
**Common femoral vein**	12 mm	113 cm^2^

**Table 2 Tab2:** Degree of stenosis based on luminal area

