### Healthcare contacts diary

Each participant will be provided with a diary following their venous ablation procedure in order to record all planned and unplanned healthcare contacts (GP visits, public health nurse visits, emergency department visits, hospital admissions, outpatient visits) and ulcer healing data. Community nursing will also report real-time ulcer healing centrally prompting clinical review. The patients will be asked to fill out the diary until their 6-month visit.

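### The primary healing outcome counts ulcers and starts its clock at the procedure, although patients are randomised and may wait weeks for treatment

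*Protocol article*

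**What the plan says.** All references are to the protocol article.

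- **Outcome.** Primary efficacy outcomes: "the proportion of ulcers healed 3 months following the overall intervention". The term for the whole intervention is not defined.
- **Unit of randomisation.** Randomisation: "Patients will be randomised to one of two groups". Statement of design: "participants allocated to one of two parallel groups in a 1:1 fashion".
- **Ulcers per patient.** Inclusion criteria admit patients "with an associated primary or recurrent lower limb venous ulcer(s) will be eligible for inclusion". An index ulcer appears only under Secondary outcomes (wound score and recurrence) and is not defined.
- **Wait.** Endovenous ablation and IVUS procedure: "The aim is for ablation within 4 weeks of randomisation". Protocol violations removes patients not ablated within 6 weeks, without saying when the 6 weeks start. Compression therapy begins at initial review in all groups.
- **Setting.** Controls are treated in ambulatory care, the intervention group in a theatre or interventional suite.
- **Early healing.** Ulcer assessment (baseline): "Ulcers that heal prior to intervention will be analysed with intention to treat".
- **Consent.** Outpatient consent is taken immediately before the procedure, and randomisation follows consent.
- **Other clocks.** Secondary outcomes count healthcare contacts and unplanned admissions over 6 months from the procedure. Healthcare contacts diary: "Each participant will be provided with a diary following their venous ablation procedure".
- **Analysis.** Statistical considerations plans intention to treat on patient outcomes, chi-square or Fisher tests for categorical data, and p < 0.05.

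**The concern.** Randomisation makes the arms comparable at the moment of allocation. An outcome timed from a later event keeps that comparability only if the event comes equally soon in both arms. Here a team member who knows the allocation arranges the procedure, and the two arms use different facilities, so the interval could differ. Compression works throughout the wait and ulcers that heal early stay in the analysis, so the arm that waits longer has more total healing time by its assessment. A patient who is never ablated has no start date, which cannot be squared with intention to treat.

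Separately, a proportion of ulcers gives a patient with two ulcers twice the weight of a patient with one. Ulcers on the same patient tend to heal or fail together, and the named tests assume independent observations.

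At stake is the healing estimate, which this phase is meant to pass on to the design of the definitive trial.

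**Working it through.** **1. The plan's own figure.** Medians of 140 and 110 days give a ratio of 110/140 = 0.786. Under Schoenfeld's formula with two-sided 5% and 80% power (both assumed, as the article states neither), events = 4 × (1.960 + 0.842)² / (ln 0.786)² = 540. This matches the stated 540 if every patient heals, and 540 × 1.1 = 594. That calculation counts patients and uses time to healing, so this point does not touch it.

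**2. Planned effect on the 3-month scale.** Assume exponential healing and 91 days.
- Control: 1 − 0.5^(91/140) = 36.3%.
- Intervention: 1 − 0.5^(91/110) = 43.6%.
- Difference: 7.4 points (7.3 at 90 days).

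**3. False difference from unequal waits, with no true effect.** Let w be the wait in days and r the healing speed before ablation relative to after it. Early-healed ulcers count as healed. Then P(healed 91 days after intervention) = 1 − 0.5^((r·w + 91)/140).

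The value r = 1 means equal speed. The value r = 0.68 is 56/82, from the medians of the early-ablation trial cited in the Discussion, and is only a rough guide. The waits are assumptions.

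| Wait, intervention v control | r | Intervention | Control | False difference |
|---|---|---|---|---|
| 4 v 2 weeks | 1 | 44.5% | 40.5% | +4.0 |
| 4 v 2 weeks | 0.68 | 42.0% | 39.2% | +2.8 |
| 5 v 2 weeks | 1 | 46.4% | 40.5% | +5.9 |
| 5 v 2 weeks | 0.68 | 43.4% | 39.2% | +4.2 |
| any equal waits | any | same | same | 0 |

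The 4 v 2 week rows lie within the protocol's 4-week aim; the 5-week rows exceed it. If controls waited longer, the sign would reverse.

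**4. The same case counted from randomisation.** At 12 weeks (84 days), P = 1 − 0.5^((r·w + 84 − w)/140).
- With r = 1 the wait cancels and the difference is 0.
- With r = 0.68 and 4 v 2 weeks, the exponents are 75.1/140 and 79.6/140. This gives 31.1% v 32.6%, or −1.5 points. That is a real consequence of later treatment, not an artefact of the clock.

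**5. Ulcers analysed as independent.** Design effect DE = 1 + (m − 1) × ICC, where m is the size-weighted mean number of ulcers per patient. Actual type I error = 2 × [1 − Φ(1.96/√DE)]. The inputs are assumptions, as the article gives no ulcer counts.
- 10% of patients with two ulcers: m = (0.9 + 4 × 0.1)/1.1 = 1.18. With ICC 0.3, DE = 1.055 and error is 5.6%.
- 30% with two ulcers: m = (0.7 + 4 × 0.3)/1.3 = 1.46. With ICC 0.5, DE = 1.23 and error is 7.7%.
- m = 1.5, ICC 0.5: DE = 1.25 and error is 8.0%.
- One ulcer each: DE = 1 and error is 5%.

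**The case against.** **Unequal waits are not documented.** A reader might infer that the arms will wait differently, so that a false difference is built in. The article does not support that. It sets one ablation target and one limit for everyone and gives no waits by arm. Outpatient consent immediately before the procedure, followed by randomisation, implies almost no wait for those patients. This objection stands, and it makes the bias conditional. It does not remove the fault: the 4-week aim, the 6-week limit and the rule for ulcers healed before intervention all presuppose a wait, and no same-day rule is given for inpatients.

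**The size depends on the scenario.** A reader might also infer that waiting alone could yield most of the planned effect. That needs a wait beyond the 4-week aim in one arm together with equal healing speed before and after ablation. At 4 v 2 weeks the artefact is 2.8 to 4.0 of 7.4 points.

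**Per-ulcer testing may not be intended.** The index ulcer in the secondary outcomes, the reference to patient outcomes and a sample size counted in patients all suggest one outcome per patient. The sentence on tests is generic. This is fair, but the primary outcome does not say so, and the index ulcer is never defined.

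**Negative healing times.** These cannot be asserted, because time to healing has no stated origin.

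**This is a 60-patient feasibility trial.** At 30 per arm and about 40% healed, the 95% interval for a difference is about ±1.96 × √(2 × 0.4 × 0.6/30) = ±25 points, far wider than the artefact. That lowers the severity. The protocol still calls this a primary outcome and uses the phase to plan the definitive trial, where a systematic shift would not average out.

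**Conclusion.** The point holds as a fault in the outcome definition, of moderate severity. The unit does not match the unit of randomisation. The time origin is a post-randomisation event that could depend on arm and does not exist for patients never ablated.

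The numerical consequences are conditional. The false difference of 2.8 to 4.0 points rests on assumed waits of 4 v 2 weeks, exponential healing with a 140-day median, and early-healed ulcers counting as healed, which the baseline section suggests but does not spell out. It is zero with equal waits or same-day randomisation. Type I error of 5.6% to 8% rests on assumed ulcer counts and ICC and on a per-ulcer analysis. The primary feasibility outcome and the stated 540/594 are unaffected.

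**What to change.** - Define the outcome as the proportion of randomised patients whose index ulcer is healed at a fixed time from randomisation, such as 12 weeks. Fix one index ulcer per patient at baseline by a stated rule, and include patients who are never ablated.
- Use randomisation as the origin for time to healing, healthcare contacts and admissions, and issue the diary then.
- Keep healing 3 months after intervention as a supportive analysis.
- Reconcile the outpatient consent and randomisation sections with the 4-week aim, the 6-week limit and the rule for ulcers healed before intervention, so that the point of randomisation is unambiguous.

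The cost is wording and visit windows. The 12-week window would contain a few weeks less follow-up after the procedure, and any real delay in treatment would count against the arm that waits longer (about −1.5 points in the 4 v 2 week case at r = 0.68).
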